# Study Schedule

**Table 2: Summary of scheduled study activities**

|  |  |  |  |
| --- | --- | --- | --- |
|  |  | **Time** | **Activities** |
|  |  |  |  |
|  |  |  |  |
| **Enrolment Visit** |  | 1st antenatal care visit at < 14 -20 weeks of gestation | - Identification of eligible mother - Enrolment - Baseline Data collection - Collection of venous blood sample - Collection of vaginal swab - Ultra Sounds examination - 1st IPTp treatment |
|  |  |  |  |
| **2nd Treatment Visit** |  | At 22-26 weeks of gestation | - 2nd IPTp treatment - Finger prick blood sample - Collection of data on net use, health seeking, etc - Collection of vaginal swab - Treatment for STIs |
|  |  |  |  |
| **3rd Treatment Visit** |  | At 28-32 weeks of gestation | - 3rd IPTp treatment - Finger prick blood sample - Collection of data on net use, health seeking, etc |
|  |  |  |  |
| **Delivery** |  | At delivery | - Health assessment of mother & child - Measurement of child’s birth weight, & maternal Hb - Collection venous blood & placental blood sample and placental specimen from mother - Cord blood collection from child |
|  |  |  |  |
| **6 Weeks Follow-up** |  | 6 weeks after delivery | - Health assessment of mother & child - Collection of heel prick blood sample from child |
| **3 months follow up** |  | 3 months post delivery (250 consecutive women) | - Health assessment of mother & child - Collection of venous blood from mother |
|  |  |  |  |
| **1 year Follow-up** |  | 1 year after delivery | - Health assessment of child |
|  |  |  |  |

A graphic representation of study activities is given in Appendix I.

## Enrolment

Upon presentation at first ANC visit, the PNGIMR study team will determine eligibility of participants (see 5.1 above for criteria) and administer written informed consent (see 14.3 for details of consent procedures).

Upon consent the baseline health assessment will be conducted and women will be assessed for the following exclusion criteria:

- chronic illness,
- symptomatic severe anaemia (Hb < 6 g/dl with symptoms such as breathlessness, weakness, dizziness), or
- permanent disability, that prevents or impedes study participation

Any one or more of the above criteria is sufficient to exclude women from study participation:

Women with severe anaemia and no, or minimal, symptoms, can be enrolled but will be treated according to local guidelines with a full course of antimalarial (SP+CQ, or SP + AZ, depending on randomisation group) and iron replacement treatment.

In the event an eligible woman is excluded from the study, the PNGIMR field study team will record the reason for exclusion in the study log book. Women diagnosed with symptomatic severe anaemia will be referred to Modilon hospital for treatment.

Enrolment and 1st treatment will be done at the same time, provided the woman is >13 weeks’ gestation.

Details of the procedures of Enrolment & 1st treatment Visit are given under 6.1 above.

Community controls will be enrolled in their villages by IMR staff, following village tok saves. Villages will be selected based on enrolment of pregnant women from these villages.

## Treatment & Follow-up Visits

**7.3.1 Treatment Visits**

Following enrolment and 1st treatment women will receive further IPTp treatments at two intervals, at least 4 weeks after the previous administration. For details of procedure see 6.1.4 b & c.

At every ANC visit, only women who spontaneously report illness to study or ANC staff will be assessed on the spot for presence of malaria infections or anaemia.

Women found to have symptomatic severe anaemia (Hb < 6 g/dl) or other severe illness will be referred to the health centre for appropriate treatment. They will not be suspended from participation in the study but will be monitored again for anaemia and clinical status at their next ANC visit. Should their condition not have resolved by that time, they will be considered chronically ill and excluded from further participation in the study.

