## Inclusion/Exclusion Criteria

Upon informed consent all eligible participants (see 5.1 above for criteria) will be screened for the following exclusion criteria:

- Known chronic illness, e.g. TB, diabetes, renal failure
- Severe anaemia requiring hospitalisation (Hb < 6 g/dl accompanied by symptoms requiring urgent treatment), or
- permanent disability, that prevents or impedes study participation and/or comprehension
- Known multiple pregnancy

Any one or more of the criteria is sufficient to exclude study participation. Women with severe anaemia (Hb <6 g/dl) but without significant symptoms can be enrolled. Anaemia will be treated according to national standard treatment guidelines. All women excluded on health grounds will be referred to Modilon Hospital, where they will be treated according to PNG national treatment guidelines.

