At the end of the enrolment visit the study team will schedule the next treatment visit with the woman. Participants will be instructed to seek medical attention immediately if they have any sign or symptoms of illness or any other condition that they deem as a threat to their well-being following the treatment. They will also be encouraged to seek medical care if they note any symptoms of malaria, fever, or illness, and to report any antimalarial treatments received or used.

1. 2nd Treatment Visit

During the 2nd treatment visit the PNGIMR study team will conduct the following tasks:

Woman:

- Interview and record
  - history of bednet use in two weeks prior
  - history of malaria treatment in two weeks prior
- Take growth measurements
  - Maternal weight
  - Fundal height
- Collect 250 µl finger prick blood sample
  - Prepare thin and thick blood smears
  - Archive a portion of the blood sample for laboratory analyses
- Check the woman’s health records booklet for recent health centre visits and record applicable information
- Measure maternal blood pressure and check for oedema. If elevated blood pressure or oedema present, women will be tested for proteinuria. Presence of all three will be considered clinical evidence of pre-eclampsia, and women will be referred for obstetric care through Modilon Hospital.
- If possible, perform second ultrasound examination for fetal growth monitoring.

Data and responses of the participant will be recorded on the 2nd Treatment Visit CRF at the time the measurements and interview are conducted. As at enrolment a thorough physical examination (including axillary temperature, measurement of Hb, etc.) will only be conducted on enrolled women who spontaneously report as ill to either the study team or the health centre staff conducting the clinic. Women diagnosed with presumptive malaria will be tested on the spot for malaria infections using a rapid diagnostic test (RDT). If the RDT is positive, they will be treated with a full course of Coartem instead of the scheduled treatment. For all women reported sick, detailed symptomatology, result of RDT and treatments given will be recorded on the ‘Morbidity Surveillance Form’.

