Data and responses of the participant will be recorded on the Final Treatment Visit CRF at the time the measurements and interview are conducted. As at enrolment a thorough physical examination (including axillary temperature, measurement of Hb, etc.) will only be conducted on enrolled women who spontaneously report as ill to either the study team or the health centre staff conducting the clinic. Women diagnosed with presumptive malaria will be tested on the spot for malaria infections using a rapid diagnostic test (RDT). If the RDT is positive, they will be treated according to PNG standard treatment guidelines with a full course of Coartem instead of the scheduled treatment. For all women reported sick, detailed symptomatology, result of RDT and treatments given will be recorded on the ‘Morbidity Surveillance Form’.

Following the collection of data and blood sample the woman will receive the Final IPTp treatment dose (if she is allocated to the SP and azithro arm of the study, or matching SP and Az placebo). Administration will be as for the second treatment dose.

At the end of the visit the field study team will remind the woman of the importance of delivering in the Health Centre or Hospital. Women who fail to attend the study ANC clinic will be contacted by the village reporters and encouraged to present at their local health centre to receive the missed treatment.

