### Specimen Collection, Preparation, Handling and Shipping

#### Instructions for Specimen Preparation, Handling, and Storage

1. **Blood Collection**
   1. Finger prick bleeds

At the second and third (where applicable) treatment dose blood samples of approximately 250 μl will be collected from each woman participating in the Protocol. Additional samples will be taken from symptomatic individuals during passive morbidity surveillance. These blood samples will be obtained by the finger prick method.

These samples will provide adequate blood for the preparation of thin/thick blood smears to detect the presence of malaria parasites, type of malaria parasites, and level of parasitemia. A portion of the sample also will be archived in a K+EDTA microtainer for laboratory analyses (e.g. serum & DNA preparation, PCR/LDR-based diagnosis of malaria parasites).

- 1. Venous blood draws

In order to have sufficiently large samples for the detailed immunological measurements detailed in the supplementary protocol, venous blood draws are needed at enrolment and delivery. The volumes of the venous draws are limited to 10 ml. Cell mediated immunology will be studied in separately funded studies.

Drawing venous blood samples will be done by specially trained staff. We will use butterfly needles of 21 gauge and heparinized vacutainers. Residual blood in the tube attached to the butterfly needle will be used to measure haemoglobin levels and make blood smears.

Venepunctures will be performed on veins in the participants’ arms. Upon removal of the needled localized bleeding is efficiently stopped with a small pressure bandage (e.g. a Band Aid). Properly done this procedure is virtually painless. However, if the needle punctures the blood vessel, there is a risk of local bleeding that can result in minor hematoma. In order to assure the safety of participants, they will be monitored following blood draw until it can be ascertained the local bleeding has stopped. Subjects will be instructed to present to the study nurses based at participating health centres in case of localized hematomas or infection at site of needle injection who will then attend to them and if necessary refer them for further treatment.

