These samples will provide adequate blood for the preparation of thin/thick blood smears, direct measurement of haemoglobin (enrolment and delivery only), DNA extraction for parasite and host genetic typing as well as provide peripheral blood mononuclear cells (PBMC’s) and parasites for in-depth immunology studies. The sample will be collected in heparinized tubes and separated into red cell, white cell and serum fractions. Samples of these fractions may be stored frozen for later laboratory analyses.

1. **Preparation of Blood Smears**

The preparation of thin and thick blood smears will be in accordance with the procedures set forth in the Field and Laboratory Procedures Manual.

1. **Determining Haemoglobin Concentration**

At enrolment and delivery, haemoglobin concentration will be determined directly in the field by using a HemoCue® device (HemoCue, Ångholm, Sweden) and will be expressed as grams of haemoglobin per decilitre. The instrument records haemoglobin concentrations to the nearest tenth of a gram per decilitre.

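### Women enrolled with Hb below 6 g/dl and few or no symptoms have no further study haemoglobin scheduled until delivery

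*Combined protocol and SAP*

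**What the plan says.** **Who may enter.** Section 5.2 excludes severe anaemia only when it needs hospital care. A woman with Hb below 6 g/dl "but without significant symptoms can be enrolled". Section 7.1 agrees: "Women with severe anaemia and no, or minimal, symptoms, can be enrolled". It adds that such women get an antimalarial course, which is their randomised first regimen, together with iron, under local guidelines.

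**When Hb is measured.** Section 6.2.3 lists, among the uses of the venous samples, "direct measurement of haemoglobin (enrolment and delivery only". Its separate paragraph on the HemoCue method names the same two time points.

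**The second and third treatment visits.** Section 6.1.4 says of the second visit that a full examination, Hb included, "will only be conducted on enrolled women who spontaneously report as ill to either the study team or the health centre staff". The third-visit text carries the same limit: "measurement of Hb, etc.) will only be conducted on enrolled women who spontaneously report as ill". For the finger-prick blood taken at these visits, section 6.2.3 states the purpose as follows: "These samples will provide adequate blood for the preparation of thin/thick blood smears to detect the presence of malaria parasites". A portion is archived. Haemoglobin is not among the listed uses.

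**The recheck rule.** Section 7.2 (subheading 7.3.1) applies the limit to every antenatal visit in these terms: "only women who spontaneously report illness to study or ANC staff will be assessed on the spot for presence of malaria infections or anaemia". Those with symptomatic severe anaemia or another severe illness "will be monitored again for anaemia and clinical status at their next ANC visit", and are excluded from further participation if they have not recovered by then.

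**The concern.** The plan knows these women's Hb at entry and treats them for it, but does not schedule a check that the treatment worked. Every later study route to an Hb starts from a complaint, a symptom or a sign. These women were not excluded precisely because they had few or none, so a symptom trigger is poorly suited to detecting non-response in them.

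Elsewhere the protocol treats the number itself as what matters. Section 11.1.1 and Appendix II define severe anaemia by Hb alone, and section 6.1.7 acts on an Hb below 6.0 g/dl found during surveillance. The Background section says that maternal anaemia predisposes to maternal mortality. Two women with the same Hb are therefore followed differently: one with symptoms is rechecked at her next antenatal visit, and one without is not.

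What is at stake is the safety of an identified subgroup, not the efficacy comparison.

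**Working it through.** The plan states no figure on this point, so there is none to reproduce. The check has two parts: tracing the routes to an Hb, and measuring the interval.

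**1. Routes to a maternal study Hb between enrolment and delivery**

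| Place | What triggers an Hb |
| --- | --- |
| 6.1.4, second and third treatment visits | The woman reports as ill |
| 7.2, every antenatal visit | The woman reports illness |
| 7.2.2, non-treatment visits | Clinic staff refer on symptoms or signs; no Hb is named |
| Study Design and 6.1.7, passive surveillance | Presentation with febrile illness, symptomatic anaemia or presumptive malaria |
| Section 9, enquiry before each dose | New symptoms or signs; no Hb is named |
| 6.2.3, Hb schedule | Enrolment and delivery |

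Scheduled study Hb readings strictly between enrolment and delivery: 0.

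**2. Does the recheck rule cover these women?** It applies to women found with symptomatic severe anaemia or other severe illness. A woman with Hb below 6 g/dl and no complaints meets neither condition. Section 7.1 gives her treatment but no repeat measurement.

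**3. Length of the interval.** First treatment is at 14 to 26 weeks (Study Design). The documents fix no gestation at delivery, so 40 weeks is an assumption, with 37 to 42 weeks as the range.

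- Delivery at 40 weeks: 40 − 26 = 14 weeks to 40 − 14 = 26 weeks.
- Range for delivery at 37 to 42 weeks: 37 − 26 = 11 weeks to 42 − 14 = 28 weeks.
- Women enrolled at or before 13 weeks: counted from enrolment, at least 40 − 13 = 27 weeks for delivery at 40 weeks.

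**4. What readings at visits 2 and 3 would change.** Visits are at least 4 weeks apart (7.2). Table 2 puts visit 2 at 22–26 weeks and visit 3 at 28–32 weeks; Appendix I has 28–34 weeks for the last window.

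- If visits fall inside these windows, the longest gaps are 26 − 14 = 12 weeks (first treatment to visit 2), 34 − 22 = 12 weeks (visit 2 to visit 3) and 40 − 28 = 12 weeks (visit 3 to delivery). The longest interval falls from 26 to 12 weeks.
- This result is conditional. With 4-week spacing, visit 2 can fall by 26 weeks only if first treatment is by 26 − 4 = 22 weeks. Women first treated later cannot meet the window.
- A woman first treated at 26 weeks could be rechecked from 26 + 4 = 30 weeks at the earliest, 40 − 30 = 10 weeks before delivery. The documents give no latest time for her.

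**5. Number affected.** The nearest figure is in the Background: 13% of women in recent local data had Hb below 7 g/dl. That is a different cut-off and does not separate women with and without symptoms. No count below 6 g/dl follows from it.

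**The case against.** The strongest reply is that the study is not these women's only source of care. Their anaemia is found at entry and treated under national guidelines (5.2) or local guidelines (7.1). Ongoing antenatal care belongs to health-centre or hospital staff under PNG standard recommendations (6.1), and those documents are not supplied. Enrolment findings go into the health booklet (6.1.4), which women carry when seeking care and which the study team reviews at scheduled visits (6.1.7). Study physicians are responsible for participants' clinical care (6.1, Field Study Team). Each of these softens the gap. None of them schedules a repeat Hb, so the statement about the study's own schedule stands, while anything about total care must stay conditional.

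The Potential Risks text also links the blood samples, including those at treatment visits, to evaluating haemoglobin. That is a general statement of purpose. Sections 6.1.4 and 6.2.3 are the operative procedures, and they do not list Hb at visits 2 and 3.

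A reader might infer more than the documents support:

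- *That these women are left untreated or unmonitored.* They are treated at entry, and routine care may re-measure Hb.
- *That the group is large, or negligible.* Neither can be shown, for the reason given in step 5 of the working.
- *That the trial result is compromised.* The primary outcome is low birth weight, and nothing in its analysis uses an Hb from visits 2 or 3.
- *That the regimen in 6.1.7 can simply be extended to these women.* It is written for women presenting ill. It does not say whether that visit's randomised dose is given, delayed or replaced, and its antimalarial courses could fall unequally between arms.

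**Conclusion.** The point holds for the study's own schedule. Women entering with Hb below 6 g/dl and few or no symptoms have no planned study Hb until delivery, and the recheck rule does not reach them. The first study reading in a woman who never complains would come about 14 to 26 weeks after first treatment if delivery is at 40 weeks, or 11 to 28 weeks across deliveries at 37 to 42 weeks. It rests on those assumed delivery dates and on routine care not repeating the Hb, which the documents neither state nor rule out.

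The plan breaks none of its own rules here. This is a design choice worth reconsidering on safety grounds, because the women are already identified and the blood is already drawn.

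**What to change.** Add to section 6.1.4 (second and third treatment visits), and reflect in 6.2.3 and 7.2:

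*Women with Hb <6 g/dl at enrolment have Hb measured by HemoCue at the 2nd and 3rd treatment visits, whether or not they report illness.*

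Use the finger-prick sample, or the 5 ml venous sample that replaces it at the third visit in the first 150 women. Then state that:

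- a repeat Hb below 6 g/dl is referred to the study physician for management under national guidelines;
- the randomised dose is given as scheduled unless the physician judges otherwise;
- any antimalarial given is recorded;
- the rule in 7.2 that excludes unresolved cases does not apply to these women, since it would add exclusions after randomisation.

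Alternatively, if routine antenatal care already re-measures Hb in these women, the sponsor could say so and cite the guideline.

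**Cost.** Up to two cuvettes and two form entries per affected woman, plus the care of any persistent severe anaemia found. No new visit, device or blood draw is needed. The real downside is that management may bring some extra non-study antimalarial courses, possibly more in one arm than the other, which would blur the treatment contrast. Its size cannot be given because the number of women affected is unknown.

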## Criteria for Discontinuation or Withdrawal of a Subject

**Participants may withdraw at any time from participation in this study.**

A participating woman will be discontinued from the study if one of the following criteria are fulfilled:

- the participant moves away from the selected study area for a period longer than 2 months
- the participant develops a chronic illness that impedes continuation in study.
- the participant displays or develops severe side effects to study drugs
- the participant dies.

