### Serious Adverse Event Detection and Reporting

For all events meeting the above described definition of Serious Adverse Events and/or Grade 4 AE, the completion of the Serious Adverse Event report form is required.

The study physicians will inform the PIs immediately of any SAE or Grade 4 AE and complete a Serious Adverse Event Form within the following timelines:

- All deaths, whether associated or not associated, will be recorded on the Serious Adverse Event Form. The Form will be sent by fax to PIs within 24 hours of site awareness of the death.
- Serious adverse events other than death, regardless of relationship, will be reported via fax by the site within 72 hours of becoming aware of the event.

Other supporting documentation of the event will supplied as requested.

The SAE Form will be reviewed by the PIs or their designate, who may request additional information or carry out further investigations. Additionally, an independent local clinician will be appointed to review all SAEs and prepare separate reports for the PIs,DSMB and Malaria in Pregnancy Consortium Safety Working Group

The Principal Investigators will notify the DSMB and Malaria in Pregnancy Consortium Safety Working Group immediately of any serious adverse event, deaths or life-threatening problems that occur in the study within 48 hours and supply all subsequent information at the earliest.

If a grade 4 event is unexplained, or is attributed to study medication, the DSMB chair will instruct the investigators to report the event to the IMR Institutional Review Board, the PNG Medical Research Advisory Committee (MRAC) and the Royal Melbourne Hospital Human Research Ethics Committee (RMH HREC). Reports to the DSMB of severe adverse events (not believed to be due to the study drug) will be submitted to the IRBs electronically on a two-monthly basis.

Reporting of data to the MiP Consortium safety working group will occur in parallel to reporting to the DSMB, e.g. by copy of email report submissions.

Subjects will be withdrawn from the study if they experience a drug related SAE / grade 4 AE.

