### Primary Outcome Measures

1. **Percentage of babies born with low birth weight**

This is the primary objective of the study and will be evaluated by assessing difference in proportion of LBW deliveries between the 2 treatment groups.

When women give birth outside of health facilities, they will be instructed to present with their newborns for checkups as soon as possible, and in any case within 7 days of delivery. Childhood immunisation will be commenced, maternal health assessed, and infant weight measured. Weight within 7 days of birth can be approximated to birth weight.

Only women who receive at least 1 IPTp treatment and have a recorded pregnancy outcome (abortion, still birth, or live birth) will be included into this analysis. This restriction applies to all analyses except for analyses of reported drug side effects (see 9. below).

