## Sample Size Considerations

The primary objective of the study is to determine the effect of IPTp with SP/AZ compared to SP/CQ clearance treatment on prevalence of low birth weight (LBW) in women using ITNs. The overall power and sample size calculations are thus based on this outcome.

The analyses for this primary outcome measure will use Poisson regression (with or without random effects). Sample size calculations for these types of analyses are non-trivial and often require extensive simulations. For that reason we are using an approximate sample size calculation based on comparison of two Poisson rates.

**Table 3**: Sample size calculations for principal outcomes using appropriate two sided tests, a significance level of 5% and a power of 80%.

|  |  |  |  |  |
| --- | --- | --- | --- | --- |
| **End points** | **Expected Outcomes** | |  | **Sample Size** |
|  | Control | AZ-SP |  |  |
|  |  |  |  |  |
|  |  |  |  |  |
| **Primary** |  |  |  |  |
| Prevalence of LBW | 12% | 8.4% |  | 1163 |
| Mean birth weight | 2.94kg | 3.01kg |  | 970 |
|  |  |  |  |  |
| **Secondary** |  |  |  |  |
| Prevalence of *P. falciparum* at delivery (peripheral & placental) by PCR | 30% | 20% |  | 389 |
| Prevalence of malaria in placental histology | 30% | 20% |  | 389 |
| Mean Hemoglobin at delivery | 10.0 | 10.3 |  | 845 |
| Prevalence of bacterial STI at 2nd/final treatment time point | 30% | 10% |  | 72 |
|  |  |  |  |  |

Previous studies suggest that IPTp with SP can increase birth weight by approximately 130 g. ITNs increase birth weight by around 60 g. The effect of adding SP to ITNs is not clear, but we assume that it increases mean birth weight by approximately 70 g. LBW is seen in 16% of babies born to women not using ITNs in PNG. If ITNs decrease LBW by 25% then we will expect 12% of babies to be LBW. SP+AZ may have additional benefits (through control of STIs which impair fetal growth) over SP alone. Our conservative estimate is that SP + AZ will decrease LBW prevalence by 30%. Based on these assumptions, a sample size of 1,163 and 970 women per arm, respectively, are required to find a 30% reduction in LBW and a 70g increase in birth weight with a power of 80% (Table 3).

Assuming, a loss of 20% during follow-up, we will thus enroll 1396 women per arm.

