## Participant Enrolment and Follow-Up

This study will enrol 2792 pregnant women over a period of 18-24 months. Enrolment and follow up will occur through Hospital and Health Centre Antenatal Clinics. Apart from some ultrasound visits (particularly at enrolment), no additional study visits will be required, beyond visits for standard antenatal care.

Currently there are high levels of ANC attendance in Madang. If women miss a treatment or follow-up visit they will be visited on the next day by a village reporter and encouraged to visit the health centre or the hospital ANC. We therefore expect >90% attendance at any follow-up time point.

However, people in the study areas do occasionally move the village of residence. In addition some people do grow tired of participating in intensive longitudinal follow up studies and withdraw consent for continued participation.

Women that missed more than 2 treatments will be excluded from all analyses except those on drug side effects. Consequently, we expect about 20% loss of follow-up.

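### Women are removed from the study, not only from treatment, for unresolved severe illness and drug reactions, with no provision to record their babies' birth weights, so the primary analysis may lose outcomes for reasons tied to arm and outcome

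*Combined protocol and SAP*

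**What the plan says.** Three rules end participation in the study rather than only treatment:

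- Section 7.2, Treatment Visits. Women found to have symptomatic severe anaemia (Hb below 6 g/dl) or other severe illness are referred and stay in the study until their next antenatal visit. Then: "Should their condition not have resolved by that time, they will be considered chronically ill and excluded from further participation in the study".
- Section 7.4. The criteria for discontinuing a woman from the study include: "the participant displays or develops severe side effects to study drugs".
- Section 9.3.1: "Subjects will be withdrawn from the study if they experience a drug related SAE / grade 4 AE".

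Section 7.3 states that no specific early termination visit is held; the date and reason are noted in the database. No section provides for recording delivery outcome or birth weight after removal, and none rules it out.

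The primary analysis set is in Section 11.1.2: "Only women who receive at least 1 IPTp treatment and have a recorded pregnancy outcome". That restriction covers every analysis except reported drug side effects. Section 11.3 adds: "Women that missed more than 2 treatments will be excluded from all analyses except those on drug side effects". Its next sentence derives an expected loss of about 20% as a consequence. The plan does not mention intention-to-treat, a method for missing birth weights or a sensitivity analysis.

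**The concern.** Stopping a drug and stopping observation are different decisions, and the plan joins them. A woman removed under these rules has no planned route to a recorded birth weight, and without a recorded outcome she leaves the primary analysis.

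On the protocol's own premises the loss may not be random. Known and Potential Benefits expects less severe anaemia on SP+AZ than on control. Background Information names maternal anaemia and LBW as joint consequences of malaria in pregnancy. Removal for unresolved severe anaemia could therefore fall more on controls, and on women at raised risk of LBW. Courses 2 and 3 are active in one arm and placebo in the other (Section 6.1), so removal for drug reactions could fall more on SP+AZ. If removal relates to both arm and outcome, randomisation no longer protects the comparison. The size and sign of the bias cannot be recovered afterwards, because the outcomes were never collected.

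The missed-treatment rule in Section 11.3 raises a second question: whom it excludes, and whether it can produce the 20% loss attributed to it.

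**Working it through.** **Planning figures.** Table 3 assumes LBW of 12% against 8.4% (risk ratio 0.084/0.12 = 0.70), two-sided 5%, 80% power, and gives 1163 per arm. The continuity-corrected two-proportion formula gives 1164, so the figure reproduces. On enrolment, Section 11.2 says: "Assuming, a loss of 20% during follow-up, we will thus enroll 1396 women per arm". That is 1163 × 1.2 = 1395.6; dividing by 1 − 0.2 would give 1454. With 20% lost, 1396 × 0.8 leaves 1116 complete women per arm, with power of 80% (78% with continuity correction).

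**Effect of removal.** Let p be the true LBW risk in an arm, q the fraction removed and r the LBW risk among those removed. Then

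observed risk = (p − q·r) / (1 − q).

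The documents give neither q nor r, so both are assumptions. Five unequal pairs were tried (control/SP+AZ: 2/1, 3/1, 1/3, 2/5 and 5/2%), with r of 20%, 30% and 40%. Example, 5% of controls and 2% of SP+AZ removed, r = 40%, true effect as planned:

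- control: (0.12 − 0.05 × 0.40)/0.95 = 0.1053
- SP+AZ: (0.084 − 0.02 × 0.40)/0.98 = 0.0776
- observed ratio: 0.0776/0.1053 = 0.74

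| Removed, control / SP+AZ | r | Observed ratio, true 0.70 | Observed ratio, true 1.00 |
|---|---|---|---|
| 2% / 1% | 20% | 0.70 | 1.01 |
| 3% / 1% | 30% | 0.72 | 1.03 |
| 5% / 2% | 30% | 0.72 | 1.05 |
| 5% / 2% | 40% | 0.74 | 1.09 |
| 1% / 3% | 30% | 0.65 | 0.97 |
| 2% / 5% | 30% | 0.62 | 0.95 |
| 2% / 5% | 40% | 0.59 | 0.92 |

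The ranges are 0.59 to 0.74 and 0.92 to 1.09. They come from these pairs and are not bounds. A 5%/1% split with r = 40% gives 0.0808/0.1053 = 0.77 (true 0.70); the reverse split gives 0.0674/0.1172 = 0.57.

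When more controls are removed, power suffers: at 1116 per arm, 5%/2% takes it from 80% to about 70% (r = 30%) or 62% (r = 40%). When more SP+AZ women are removed, the effect is exaggerated.

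**Missed-treatment rule.** There are three courses (Study Design), so missing more than two means missing all three. Staff dispense the first dose directly (Section 6.1.4), and the envelope is opened immediately before treatment (Section 6.3.3). Almost nobody can meet the criterion. As written, it agrees with the at-least-one-treatment rule in Section 11.1.2. Section 11.3 expects more than 90% attendance at any time point. At 90%, the probability of missing both later visits is 0.1 × 0.1 = 1% if visits are independent, and at most 10% under any dependence. Neither gives 20%. Missing at least one later visit would give 1 − 0.9² = 19%, but excluding those women is not what the text says and would contradict Section 11.1.2.

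**The case against.** The strongest reply is that few women may be removed. Removal for anaemia needs haemoglobin below 6 g/dl with symptoms, spontaneous reporting of illness, and failure to resolve by the next visit; women with symptomatic severe anaemia are already excluded at enrolment. Potential Risks puts severe events due to SP or AZ at fewer than 1 in 10,000, which is fewer than 0.3 of 2792 women. The 5% used above, about 70 of 1396 women, has no support in the documents. This stands as a limit on size, although the other-severe-illness and severe-side-effect criteria are broader and unquantified.

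It is also fair that loss of birth weight is inferred. Section 7.3 omits a termination visit but does not forbid later recording. The inference remains the natural reading of removal from the study.

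Three stronger readings are tempting and not supported:

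- A reader might infer that missed courses also remove women from the study. Section 11.3 excludes them from analyses only; they stay in follow-up, and the rule as worded touches almost nobody.
- A reader might infer that the plan hides drug harm. Side-effect analyses are exempt from the restriction (Section 11.1.2) and count all reported effects whatever the number of courses (Section 11.1.3). Serious events are followed until resolved, chronic or stable (Section 9.3.3), and Section 11.1.3 counts all deaths. What survives is narrower: Section 11.1.2 exempts only side effects, so read literally a woman who dies undelivered would leave the mortality analysis, in conflict with Section 11.1.3.
- A reader might infer that the bias must mask benefit. Anaemia and drug-reaction removals may act in opposite directions, and the net sign is unknown.

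Finally, the 20% need not rest on the missed-treatment rule alone, because Section 11.3 has just mentioned moving away and withdrawn consent. That is possible, but the text links the figure to the rule.

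**Conclusion.** The point holds in this form. Sections 7.2, 7.4 and 9.3.1 end study participation where only a treatment decision is needed. With Sections 7.3 and 11.1.2, that would probably drop these women from the primary analysis, and the protocol's own expectations make dependence on arm and outcome plausible.

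The size is not known. Under the assumed rates, a planned ratio of 0.70 is typically shifted by a few hundredths and at the extreme tried by 0.11 (0.70 to 0.59); a null ratio moves by at most about 0.09. If removals are around 1–2% per arm, or the removed women's LBW risk is close to the average, the effect is negligible. The case for change is that the bias is avoidable cheaply beforehand and cannot be repaired afterwards.

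The missed-treatment rule is a separate, smaller matter: as worded it causes essentially no bias, but its intended threshold and the basis for the 20% are unclear.

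**What to change.** 1. In Sections 7.2, 7.4 and 9.3.1, separate stopping study treatment from stopping follow-up. The clinical decision on treatment stays as it is. State that delivery outcome and birth weight are recorded for every randomised woman who has not withdrawn consent, and make Section 7.3 consistent.
2. In Sections 11.1.2 and 11.4.1, define the primary analysis as all randomised women with a birth weight, analysed as allocated. This is still an available-case set and, since almost every randomised woman gets a first course, close to the current one. The gain comes from collecting the outcomes. Add a pre-specified sensitivity analysis for missing birth weights that varies the assumed LBW risk by arm, and report removals by arm and reason.
3. In Section 11.3, delete the missed-treatment exclusion or keep it as a sensitivity set. Justify the 20% by expected missing birth weights.
4. Reconcile Section 11.1.2 with Section 11.1.3 so that all deaths among randomised women, and among their fetuses and infants, enter the mortality analyses.

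The cost is protocol and analysis-plan wording plus a small amount of extra delivery follow-up. The village reporters (Field Study Team) and the mobile weighing team (Section 8.1.1) already exist for this.
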